### Objectives {7}

The main goal of phase I is to assess the safety, toxicity, and maximum tolerated dose (MTD) of the Esperanza extract in patients diagnosed with metastatic gastric tumors and acute leukemias. In phase II, the focus shifts to evaluating the safety of the extract and examining its impact on improving patients' quality of life using the QLQ-C30 scale for gastric tumors. Additionally, in the context of acute leukemias during phase II, the emphasis remains on determining the safety of the extract and investigating its potential to enhance the rate of remission during induction therapy and/or facilitate hematological recovery.

In addition to the primary objectives, there are important secondary objectives for gastric tumors. One of these is to evaluate the influence of the Esperanza extract on progression-free survival and clinical response, which will be assessed using the RECIST 1.1 criteria. For acute leukemias, the assessment will focus on event-free survival, defined as the duration from enrolment to disease progression, including local or distant recurrence, second primary malignancy, primary malignancy-related death, or death from any cause, whichever comes first. Furthermore, a thorough evaluation of the impact on patients' quality of life will also be conducted.

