### Intervention description {11a}

#### Phase I treatment:

Patients who meet the inclusion criteria and have metastatic gastrointestinal tumors (colon, pancreas, stomach, and bile ducts) or newly diagnosed acute leukemias will initiate treatment with 1000 mg of Esperanza extract daily, divided into two doses of 500 mg, for a duration of 4 weeks. In the event of toxicity, the dose level will be adjusted accordingly. If toxicity occurs, the next dose level will be reduced to 500 mg using the same dosing schedule, and if there is no toxicity after 4 weeks, the dose will be increased to 2000 mg. This dose adjustment will be conducted with the same group of patients, both for escalation and de-escalation, who have completed the previous dose level, ensuring a total treatment duration of 8 weeks. The administration of the phytomedicine Esperanza will continue throughout the intervention period, without interruption, for the entire 8-week treatment duration, unless there is clinically significant toxicity that meets the investigator's criteria for discontinuing the intervention. Table 1 provides a comprehensive list of the activities to be carried out during the patients' intervention.

**Table 1 Tab1:** Schedule of activities for phase ib to evaluate safety and MTD in gastrointestinal tumors and acute leukemias

Schedule of activities				
	**Enrollment**	**Initial Visit and chemotherapy cycle 1**	**Cycle 2**	**Close-out**
**Time point**	**Week 1**	**Week 2**	**Week 6**	**Week 7**
Enrolment				
Screening and Informed Consent	X			
Physical Examen		X	X	X
Clinical Record		X	X	X
HIV Test and Pregnancy test	X			

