**Interventions**				
Medication dispensing		**X**	**X**	**X**
Follow-up visit		**X**	**X**	**X**

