### Strategies to improve adherence to interventions {11c}

All participants are scheduled for regular follow-up visits, during which a medication count is conducted to assess adherence rates. In addition, participants can address any questions they may have, and the evaluation of adverse effects that occurred during the intervention is performed. Furthermore, a telephone follow-up is carried out weekly, ensuring that participants can directly contact the coordinator to seek clarification, resolve doubts, or report any abnormal clinical signs they may be experiencing.

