### Provisions for post-trial care {30}

All participants will be monitored for a period of 1 month following the completion of their treatment. Additionally, after their final visit, participants will be informed that they have the option to seek clarification or report any new signs or symptoms through telephone or in-person consultations. Furthermore, patients will continue to receive regular clinical follow-up for their underlying disease, adhering to the established schemes and protocols at the Hospital.

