### Adverse event reporting and harms {22}

The investigator will actively monitor all study subjects for any occurrence of adverse events (AEs), both clinically and through laboratory tests, throughout the study period. Detailed documentation will be made for each AE, including the date of onset, diagnosis (if known) or presenting signs/symptoms, severity, duration (end date, ongoing, intermittent), relationship to the study drug, and actions taken in response. While it is not expected, in the event of pregnancies, comprehensive follow-up will be conducted after obtaining informed consent from the pregnant women and for data collection on both the mother and the newborn. For serious adverse events (SAEs) that are of an intermittent nature, they must demonstrate similarity in terms of their nature and severity. All adverse events will be recorded, whether prompted by specific questions, observed by the center's staff, or self-reported by the subjects themselves.

Monitoring of adverse events will continue until the resolution of each event (if it is expected to resolve) or until the clinical staff determines that it is appropriate within a 4-month period following the onset of the adverse event. Any serious adverse events (SAEs) experienced by study participants and directly related to the therapeutic intervention using the Esperanza extract must be promptly reported. The reporting of adverse events and the grading of their severity will adhere to the NCI CTCAE v5 guidelines.

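### Table 1 closes phase I at Week 7, but eight uninterrupted weeks of dosing from Week 2 end at about Week 10, so the second dose level has no dated end-of-level laboratory panel or ECG

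*Protocol article*

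**What the plan says.** In the Protocol article, section Intervention description {11a}, Phase I treatment, patients start on 1000 mg of extract daily for 4 weeks. The same patients then move to 500 mg if there was toxicity, or to 2000 mg if there was none, "ensuring a total treatment duration of 8 weeks". Dosing continues "without interruption, for the entire 8-week treatment duration", unless clinically significant toxicity leads the investigator to stop it. The section closes by pointing to the schedule: "Table 1 provides a comprehensive list of the activities to be carried out".

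Table 1 has four time points:
- Week 1: enrolment only.
- Week 2: initial visit and chemotherapy cycle 1, with the first mark for "Medication dispensing".
- Week 6: cycle 2.
- Week 7: close-out.

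The physical examination, the laboratory panel and the ECG are marked at Weeks 2, 6 and 7 and at no later time.

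Three other sections bear on monitoring:
- Adverse event reporting and harms {22} requires adverse events to be monitored "both clinically and through laboratory tests, throughout the study period".
- Strategies to improve adherence to interventions {11c} provides regular follow-up visits at which adverse effects are evaluated, and says that "a telephone follow-up is carried out weekly".
- Provisions for post-trial care {30} states: "All participants will be monitored for a period of 1 month following the completion of their treatment".

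**The concern.** The dosing period in the text is longer than the visit schedule in the table. Table 1 dates the last phase I safety tests, so a site that follows it would close a patient out while, by the text, the patient is still partway through the second dose level.

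Objectives {7} makes safety, toxicity and the MTD the main goal of phase I, and the MTD is the dose given in phase II. If patients escalate, the second level is 2000 mg and is the candidate MTD. The Week 6 panel closes the first level, but no dated panel closes the second. The end-of-phase-I safety analysis (Interim analyses {21b}) would still have adverse events from the undated monitoring. It would lack a common end-of-level panel and ECG at the dose that matters most. A laboratory or ECG change arising late in that level could be tested at different times in different patients, or missed if it gave no symptoms.

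**Working it through.** **Inputs**
- Length of each dose level: 4 weeks. Total: 8 weeks, uninterrupted (Phase I treatment text).
- First dispensing: Week 2. Cycle 2: Week 6. Close-out: Week 7 (Table 1).
- Dose step at the second cycle (Sample size {14}), which places the dose change at Week 6.

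**Does the stated duration add up?** Two levels of 4 weeks: 4 + 4 = 8 weeks. Yes. The gap from Week 2 to Week 6 in Table 1 is also 4 weeks, so the table agrees with the text on the first level.

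**Does the close-out date follow?** Expected close-out = start week + duration.
- Start at Week 2: 2 + 8 = Week 10.
- Second level from Week 6 for 4 weeks: 6 + 4 = Week 10.
- Start at Week 1, which Table 1 does not support because Week 1 has no dispensing: 1 + 8 = Week 9.

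No starting point gives Week 7. From Week 2 to Week 7 is 7 − 2 = 5 elapsed weeks, or 6 if Week 7 is counted whole, against the 8 stated.

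**Do the other tables follow start plus duration?** Table 2 has about 12 weeks of dosing from Week 2, and 2 + 12 = 14 lies within its close-out window of Weeks 12 to 14. In Table 3, newly diagnosed leukemia has 4 weeks from Week 2, and 2 + 4 = 6 matches the footnoted close-out at Week 6. Table 1 is the one that does not reconcile. The Week 10 column in Table 3 is not used as the benchmark here; the 8-week text alone gives Week 10.

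**Time after the last dated panel and ECG**

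| Dosing counted from | Second level occupies | Visit at start of Week 7 | Visit at end of Week 7 |
|---|---|---|---|
| Week 2 | Weeks 6 to 9 | 3 weeks left | 2 weeks left |
| Week 1 | Weeks 5 to 8 | 2 weeks left | 1 week left |

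- From Week 2, as a share of the second level: 2/4 = 50% to 3/4 = 75%. As a share of all dosing: 2/8 = 25% to 3/8 = 37.5%.
- From Week 1, as a share of the second level: 1/4 = 25% to 2/4 = 50%. As a share of all dosing: 1/8 = 12.5% to 2/8 = 25%.
- With close-out at Week 10: none.

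If the Week 6 panel is drawn before the dose changes, Week 7 is the only dated panel on the second level, 1 to 2 weeks in.

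**Supporting detail.** Table 1 also marks dispensing at the Week 7 close-out, so it does not show dosing stopping there. Tables 2 and 3 mark dispensing at close-out too, so this carries little weight.

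**The case against.** The strongest reply is that Week 7 is a slip in one table cell. The text states the 8-week duration twice, and staff who read it would go on seeing patients until dosing ended. Other provisions also apply: adverse event monitoring that includes laboratory tests throughout the study, regular visits with adverse event evaluation, weekly calls, and a month of monitoring after treatment.

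Most of this stands. A misprint is plausible, and these provisions make the practical risk modest. A reader might infer from Table 1 that patients go unmonitored in the last weeks of phase I, or that treatment is cut short at Week 7. The documents support neither inference: the undated monitoring continues, and the text is explicit that dosing runs for 8 weeks.

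The reply does not remove the contradiction. None of these provisions dates a panel or ECG at the end of the second level, and the adverse event section does not name ECG. Nor is this a detail that an article leaves to the full protocol, because the article itself states both figures.

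It might also be said that phase II, with its end-of-cycle safety evaluations, would catch what phase I missed. Table 2 does not bear that out. It marks the laboratory panel and ECG only at Week 2 and close-out, and phase II begins after the dose has been chosen.

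**Conclusion.** The point holds as an internal inconsistency: the Week 7 close-out in Table 1 is wrong against the 8 weeks of dosing in the same section. With dosing from Week 2, as Table 1 shows, 2 to 3 of the 4 weeks at the second level (50% to 75%) have no dated laboratory panel or ECG. Counting from Week 1 leaves 1 to 2 weeks (25% to 50%). The range depends on whether the visit falls at the start or the end of Week 7. That the uncovered dose is 2000 mg assumes that patients escalate.

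The error should be fixed, because the cell governs when the phase I safety data behind the MTD are collected. It is a scheduling error and not evidence that patients go without safety monitoring.

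**What to change.** Set the Table 1 close-out, with its full safety battery (examination, laboratory panel and ECG), at Week 10. Preferably keep Week 7 as an interim visit, so that there is a dated check soon after a possible doubling of the dose.

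**Cost.** Close-out moves by 10 − 7 = 3 weeks in either case.
- Changing only the cell adds no visit, but leaves no dated check between Weeks 6 and 10, the 4 weeks after the dose change.
- Keeping Week 7 and adding Week 10 costs one more visit and panel per phase I patient. That is 6 × 1 = 6 if the phase I sample is 6 overall, or 2 × 6 × 1 = 12 if it is 6 per tumor group. Sample size {14} can be read either way.

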**Interventions**				
Medication dispensing		**X**	**X**	**X**
Follow-up visit		**X**	**X**	**X**
**Safety Assessment**				
Hemogram		X	X	X
Transaminase AST		X	X	X
Transaminase ALT		X	X	X
Alkaline Phosphatase		X	X	X
Total Bilirubin		X	X	X
Triglycerides		X	X	X
Total Cholesterol		X	X	X
Blood Urea Nitrogen (BUN)		X	X	X
Creatinine		X	X	X
Urinalysis		X	X	X
Uric Acid		X	X	X
LDH (Lactate Dehydrogenase)		X	X	X
Lactic Acid		X	X	X
Ferritin		X	X	X
Albumin		X	X	X
Iron		X	X	X
Electrocardiogram		X	X	X
Echocardiogram				

#### Phase II treatment:

For patients with metastatic gastrointestinal tumors (colon, pancreas, stomach, and bile ducts), a total of 30 new patients will be enrolled and divided into two groups: an intervention group and a placebo group, each consisting of 15 patients. The intervention group will receive continuous treatment with the Esperanza extract at the determined maximum tolerated dose (MTD) for three treatment cycles, equivalent to approximately 12 weeks. The placebo group will receive a placebo in addition to standard chemotherapy treatment for their underlying disease. Safety evaluations will be conducted at the end of each treatment cycle, and the efficacy evaluation will be carried out after completion of the three treatment cycles. Table 2 provides a comprehensive list of the activities to be carried out during the patients' intervention.

**Table 2 Tab2:** Activity schedule for phase II clinical trial in gastrointestinal tumors

Schedule of activities					

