**Safety Assessment**					
Hemogram		X			X
Transaminase AST		X			X
Transaminase ALT		X			X
Alkaline Phosphatase		X			X
Total Bilirubin		X			X
Triglycerides		X			X
Total Cholesterol		X			X
Blood Urea Nitrogen (BUN)		X			X
Creatinine		X			X
Urinalysis		X			X
Uric Acid		X			X
LDH (Lactate Dehydrogenase)		X			X
Lactic Acid		X			X
Ferritin		X			X
Albumin		X			X
Iron		X			X
Electrocardiogram		X			X
Echocardiogram		X			X

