**Efficacy Assessment**					
RECIST		X			X
Tumor Antigens		X			X
CA199		X			X
ACE		X			X
Metabolome		X		X	X
Microbiome Analysis		X			X
Proinflammatory Cytokines		X		X	X
Circulating DNA		X		X	X
Ketone Bodies		X		X	X
Tumor Infiltration		X			X
QLQ C-30 Quality of Life Surveys		X	X	X	X
Progression-Free Survival		X			X

For newly diagnosed acute leukemias, a total of 28 new patients will be recruited, and an additional six patients will be recruited for the relapsed leukemias group. Both groups will receive continuous treatment with the Esperanza extract at the determined MTD for four weeks. Standard chemotherapy treatment for their underlying disease will be administered to both groups. At the end of the treatment cycle, safety and efficacy evaluations will be conducted. Table 3 provides a comprehensive list of the activities to be carried out during the patients' intervention.

**Table 3 Tab3:** Activity schedule for phase II clinical trial in acute leukemias

Schedule of activities				

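### Phase II gastrointestinal part: the text promises a safety evaluation after every cycle, but Table 2 schedules no safety tests between Week 2 and close-out at Week 12-14

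*Protocol article*

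**What the plan says.** The section on phase II treatment gives the extract or placebo alongside chemotherapy for "three treatment cycles, equivalent to approximately 12 weeks". On safety it states: "Safety evaluations will be conducted at the end of each treatment cycle". It then points to the schedule: "Table 2 provides a comprehensive list of the activities".

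Table 2 has visits at Week 2 (start of cycle 1), Week 6 (cycle 2), Week 10 (cycle 3) and close-out at Week 12-14. Its "Safety Assessment" block has 18 rows, each marked at Week 2 and close-out only. Physical examination, clinical record and follow-up visit are marked at all four visits.

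Two other sections bear on the point. Section {22}, on adverse event reporting, requires subjects to be monitored "both clinically and through laboratory tests, throughout the study period", without fixing time points. Section {11c}, on adherence, says that at follow-up visits "the evaluation of adverse effects that occurred during the intervention is performed", and adds weekly telephone contact.

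**The concern.** The sentence and the table do not agree on when safety is assessed, and a site following the table would draw no protocol-scheduled safety bloods during most of the exposure.

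This affects both patients and the analysis:

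- **Patient protection.** Section {11b} allows withdrawal for CTCAE grade 3 or higher toxicity, and suspension for clinically significant elevations below that. Silent hepatic, renal or hematological changes cannot be graded without a test. Eligibility admits patients with transaminases and alkaline phosphatase up to 5 times, and bilirubin up to 3 times, the reference value, and with a GFR just above 30 mL/min.
- **The placebo comparison.** This is the only part of the trial with a concurrent control. If mid-treatment results come only from whatever tests happen to be done, they are not secured at the same times in both arms.
- **Missing data.** The statistical methods use complete cases without imputation. A patient who leaves before close-out has no scheduled post-baseline panel at all. With 15 patients per arm, each such loss removes 1/15 = 6.7% of an arm.

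**Working it through.** No figure of the plan needs reproducing. The check is a cell-by-cell reading of the schedules.

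**Are the blank cells real?** Other rows of Table 2 use the middle columns. QLQ-C30 is marked at Weeks 2, 6, 10 and close-out. Four research assays (metabolome, proinflammatory cytokines, "Circulating DNA" and ketone bodies) are marked at Week 10. The columns are intact, so the blanks in the safety rows are not an extraction fault.

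**Safety rows marked at each visit**

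| Schedule | Week 2 | Week 6 (cycle 2) | Week 10 (cycle 3) | Close-out |
|---|---|---|---|---|
| Table 1, phase I | 17 of 18 | 17 of 18 | no such visit | 17 of 18 (Week 7) |
| Table 2, phase II gastrointestinal | 18 of 18 | 0 of 18 | 0 of 18 | 18 of 18 (Week 12-14) |

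The row that is blank in Table 1 is the echocardiogram.

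**End-of-cycle points covered.** Assume treatment starts at Week 2 and cycles last 12/3 = 4 weeks. Cycles then end at Weeks 6, 10 and 14. Counting close-out as the third point, the panel is scheduled at 1 of 3.

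**Interval between scheduled panels**

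- Now: 12 − 2 = 10 weeks to 14 − 2 = 12 weeks. Against about 12 weeks of treatment this is 10/12 = 83% to 12/12 = 100%.
- With Weeks 6 and 10 added: 6 − 2 = 4, 10 − 6 = 4, and 12 − 10 = 2 to 14 − 10 = 4. The longest interval is 4 weeks.

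**What phase I will already have shown.** Each phase I dose level lasts 4 weeks: "if there is no toxicity after 4 weeks, the dose will be increased to 2000 mg". Total phase I treatment is 8 weeks. Phase II gives the MTD for about 12 weeks, which is 12/4 = 3 times the time at any one phase I dose level and 12/8 = 1.5 times the total phase I exposure. On either count, phase II goes past the duration that phase I covers.

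**The case against.** The strongest reply is that a safety evaluation need not mean a laboratory panel. Table 2 does schedule a physical examination and follow-up visit at Weeks 6 and 10, and section {11c} places adverse-effect review at follow-up visits. Read that way, sentence and table agree. This stands in part: clinical safety observation is not absent. It does not remove the conflict. The table's own safety block consists entirely of tests, the table is called comprehensive, and section {22} names laboratory tests as part of monitoring throughout the study.

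A second reply is that laboratory monitoring is the investigator's duty under section {22}, that chemotherapy patients probably have routine bloods, and that missing data will be sought in the hospital laboratory database. Routine results may well exist. But nothing fixes their timing or requires their entry in the eCRF for Weeks 6 and 10, and a test that was never scheduled does not count as missing.

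A third is that phase I is dose-finding and may properly be tested more densely, and that Table 3 for leukemia also has only baseline and close-out panels. A lighter phase II schedule is a legitimate choice, but the text would then have to say so. Nor is Table 3 a close parallel: for newly diagnosed leukemia close-out is at Week 6, so the interval is 6 − 2 = 4 weeks.

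Two limits on the criticism are fair. Close-out at Week 12 would fall up to two weeks before a third cycle ending at Week 14, so the last panel may come slightly before exposure ends. And the choice of a minimum set of rows is a judgment, not something the documents dictate.

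**Conclusion.** The point holds and should be fixed. Table 2 does not deliver the safety evaluation that the text promises after each cycle: the test panel is scheduled at 1 of 3 points, with 0 of 18 rows marked at Weeks 6 and 10 and an interval of 10 to 12 weeks. The finding is confined to laboratory tests, electrocardiogram and echocardiogram.

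It rests on two assumptions: cycles of about 4 weeks starting at Week 2, and Table 2 being the full schedule, as the article says it is. How much toxicity would go undetected cannot be stated from the documents, because adverse-event recording and clinical visits continue and routine blood tests may be done.

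**What to change.** In Table 2, mark the laboratory safety rows at Week 6 and Week 10, as Table 1 does at cycle 2. A reasonable minimum is nine rows: hemogram, AST, ALT, alkaline phosphatase, total bilirubin, BUN, creatinine, LDH and lactic acid. State that routine pre-chemotherapy results from the hospital laboratory system may be entered in the eCRF for these time points. If electrocardiogram and echocardiogram are to stay at baseline and close-out, reword the sentence on end-of-cycle evaluation to say so.

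The cost is 9 × 2 = 18 added marks and at most 30 × 2 = 60 sampling occasions, fewer where routine bloods serve, plus data entry. The visits already exist, and the four research assays are already scheduled at Week 10.

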**Gastrointestinal Tumors**					
	**Enrollment**	**Initial Visit and chemotherapy cycle 1**	**Cycle 2**	**Cycle 3**	**Close-out**
**Time point**	**Week 1**	**Week 2**	**Week 6**	**Week 10**	**Week 12 -14**
Enrolment					
Screening and Informed Consent	X				
Physical Examen		X	X	X	X
Clinical Record		X	X	X	X
HIV Test and Pregnancy test	X				
**Interventions**					
Medication dispensing		**X**	**X**	**X**	**X**
Follow-up visit		**X**	**X**	**X**	**X**
